## Abstract

**Background::**

Atopic dermatitis (AD) is a chronically relapsing inflammatory skin disease that affects the quality of life in patients with AD. Since there is limitation of conventional treatment of AD, complementary treatment is required to treat AD symptoms more effectively and safely Soshiho-tang (SSHT) is a traditional herbal medicine that exhibits anti-inflammatory and anti-ulcer effects and improves the immune function. In this clinical trial, we will evaluate the efficacy and safety of SSHT in patients with AD and gastrointestinal disorders in comparison with placebo.

**Methods/design::**

This study is a single-center, randomized, double-blind, placebo-controlled, and investigator-initiated clinical trial. A total of 60 patients aged 3 to 18 years with AD and gastrointestinal disorders and who received a diagnosis of AD by Hanifin & Rajka criteria with a Scoring Atopic Dermatitis (SCORAD) index between 15 and 49 will be enrolled. Participants will be randomly assigned to the SSHT or placebo group in a ratio of 1:1. Additionally, they will have a visit schedule comprising 4 visits including a screening visit during 8 to 10 weeks. The participants will be administered SSHT or placebo 3 times a day for 4 weeks. The primary outcome will be measured by a change of the SCORAD index. The secondary outcome measures include the following: survey questionnaires for the perception of gastrointestinal disorders, amount and frequency of ointment usage for AD, dermatology quality of life index, itchiness and sleep disability score in visual analog scale, percutaneous water loss, skin surface temperature, Hamilton anxiety rating scale, and children's depression inventory.

**Discussion::**

In our knowledge, this will be the first clinical trial to assess the efficacy and safety of SSHT in patients with AD and gastrointestinal disorders. The findings of this study will provide new treatment options for patients with AD and gastrointestinal disorders.

**Trial registration::**

Korean National Clinical Trial Registry, Clinical Research Information Service. (KCT0003713) https://cris.nih.go.kr/cris/search/search_result_st01_en.jsp?seq=13489<ype=&rtype=

## Introduction

1

Atopic dermatitis (AD) is a chronically relapsing inflammatory skin disease which is characterized by pruritus, erythema, weeping from scratching, edema and lichenification.^[1,2]^ The worldwide prevalence of AD ranges from 5% to 20% among children aged 6 to 7 and 13 to 15 years and it is observed to be increasing in some parts of Africa, East Asia, and Western Europe for the last 20 years.^[3,4]^ With increasing prevalence of the disease, the socioeconomic burden of AD has been increasing.^[5]^

AD is a multifactorial disease caused by combination of mutations in the filaggrin gene, disrupted skin barrier, environmental factors, diet, and gut microbiota diversity.^[6,7,8]^ Although AD is not a life-threatening disease, children with AD often experience psychological and social difficulties including sleep disturbance, lack of concentration during the daytime, and isolation in school which can result in poor self-esteem, depression, frustration, as well as skin problems.^[9,10]^ It also has negative impact on the health-related quality of life of children with AD and their families.^[11,12]^ Moreover, 50% of children who were diagnosed with AD in their school-age show persistent AD in their adulthood.^[13]^

For the treatment of AD, topical corticosteroids, topical calcineurin inhibitors, barrier-enhancing creams, and systemic therapy are widely used depending on the severity of the symptoms.^[14]^ However, discontinuity in the treatment often results in relapse of the disease and several patients do not respond well to conventional treatments. Moreover, the use of long term systemic treatments can cause severe side effects including hyperglycemia, osteoporosis, renal toxicity, hypertension, and hepatotoxicity.^[7,15]^ Due to the limitations of conventional treatments, traditional herbal medicines have been increasingly used in the treatment of patients with AD.^[16]^

### Soshihotang

1.1

Soshiho-tang (SSHT, Xiao-chai-hu-tang in China and Syo-saiko-to in Japan) is a traditional herbal medicine which is composed of 7 herbal components: Bupleuri Radix, Pinelliae Rhizoma, Rhizoma Zingiberis Recens, Scutellariae Radix, Zizhyphi Fructus, Glycyrrhizae Radix et Rhizoma, and Ginseng Radix.^[17]^ Although it has been primarily used to treat liver diseases including chronic hepatitis, hepatic cancer, and bronchial asthma,^[18]^ numerous clinical and experimental studies have demonstrated that SSHT exhibits anti-inflammatory effects by increasing the blood corticosterone level,^[19]^ improves immune function,^[20]^ and shows anti-ulcer effects by inhibiting gastric secretions.^[21]^ In our previous case report, we showed that SSHT displays the potential to treat AD with gastrointestinal disorders.^[22]^ Since there was no clinical trial, we designed a randomized, double-blinded, and placebo-controlled trial to investigate the efficacy and safety of SSHT on patients with AD and gastrointestinal disorders.

### Study aims and hypothesis

1.2

The primary aim of this study is to evaluate the efficacy and safety of SSHT versus placebo for the treatment of AD patients with gastrointestinal disorders in randomized clinical trials. We hypothesize that SSHT is more effective than placebo for the treatment of AD patients with gastrointestinal symptoms. To assess the efficacy and safety of SSHT, a randomized, double-blinded, and placebo-controlled trial will be conducted.

## Methods

2

### Study design

2.1

This clinical trial is designed as a single-center, randomized, double-blind, placebo-controlled, and investigator-initiated clinical trial. A total of 60 eligible participants will be divided equally into 2 groups: SSHT group and the placebo group. Participants will be administered SSHT or placebo 3 times day for 4 weeks. At weeks 4 and 8 (follow-up time points), participants will be instructed to visit the trial center for assessment of the efficacy and safety (including adverse events). The primary outcome for assessment of the efficacy and safety of SSHT is the Scoring Atopic Dermatitis (SCORAD) index, which is used to evaluate the severity of AD. The secondary outcome measures include the following: survey questionnaires for the perception of gastrointestinal symptoms, amount and frequency of ointment usage for AD, dermatology quality of life index, itchiness and sleep disability score in visual analog scale (VAS), percutaneous water loss, and skin surface temperature. The detailed schedule and assessments conducted throughout the clinical trial are summarized in Figure 1 and Table 1. The protocol (version 1.1, 8 April 2019) follows the Standard Protocol Items: Recommendations for Interventional Trials (SPIRIT) guidelines.

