### Sample size calculation

2.7

As the primary outcome to evaluate the efficacy of SSHT in patients with AD experiencing gastrointestinal disorders, this study will use the SCORAD scores. We calculated the sample size based on the previous study which evaluated the efficacy of Shiho Cheong gan-san for patients with AD.^[23]^ It is hypothesized that the mean changes of the SCORAD score in the SSHT and placebo groups after 4 weeks of intervention were 13.8 (μt) and 7.9 (μ*c)*, respectively and the standard deviations of the SCORAD scores between 2 groups were 8.2. A total of 60 participants, 30 in each group, are needed to achieve a statistical power of 80%, significance level of 0.05 in 2-tailed test, based on an estimated 20% dropout rate.

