### Safety assessment

2.10

The data for safety assessment of the trial product will be based on the safety group. The safety population (SP) group is composed of all participants who will undergo at least 1 intervention and post-intervention safety assessment.

Adverse events: either the Chi-square or Fisher exact test will be performed to compare the differences between groups, and a summary sheet for each body organ will be created. In addition, the incidence rate of adverse events that are confirmed to be associated with either the trial product or the placebo product will be comparatively assessed using the same method.Laboratory test values: after completion of the trial, the fraction of incidences that exhibit clinical test values exceeding the normal range will be assessed using either Chi-square or Fisher exact test.Vital signs: means and standard deviations for blood pressure and heart rate will be recorded at each visit. Furthermore, significant changes in the categories of vital signs between the start and the end of the intervention will be assessed using either paired *t* tests or Wilcoxon signed rank tests.

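### SCORAD is named as the primary outcome for safety as well as efficacy, and the planned between-group safety test in at most 30 per arm says little when it is non-significant

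*Protocol article*

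**What the plan says.** Section 1.2 (Study aims and hypothesis) joins the two objectives: "The primary aim of this study is to evaluate the efficacy and safety of SSHT versus placebo". The hypothesis that follows concerns efficacy alone: "We hypothesize that SSHT is more effective than placebo for the treatment of AD patients with gastrointestinal symptoms".

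Section 2.1 (Study design) then gives both objectives one outcome: "The primary outcome for assessment of the efficacy and safety of SSHT is the Scoring Atopic Dermatitis (SCORAD) index". The same sentence describes SCORAD as an index "which is used to evaluate the severity of AD". No adverse-event or laboratory measure appears among the primary or secondary outcomes, either there or in the Abstract.

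Section 2.7 (Sample size calculation) ties the index to efficacy: "As the primary outcome to evaluate the efficacy of SSHT in patients with AD experiencing gastrointestinal disorders, this study will use the SCORAD scores". The 30 per arm are derived from SCORAD change only.

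Section 2.10 (Safety assessment) defines a safety population and covers adverse events, laboratory values and vital signs. For adverse events, "either the Chi-square or Fisher exact test will be performed to compare the differences between groups". Product-related events are handled in the same way, and the same two tests are named for out-of-range laboratory values. Vital signs are compared before and after treatment by paired tests. Section 2.13 schedules blood and urine tests at screening and week 4, and an adverse-event interview at week 8.

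**The concern.** Two things do not fit together.

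First, a severity score carries no information on adverse events or laboratory toxicity. Read literally, section 2.1 leaves the safety part of the primary aim without a valid named outcome, and it disagrees with sections 2.7, 2.10 and 2.13.

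Second, the between-group method fixed for safety is a significance test in a trial sized on SCORAD. A significant excess of events would be informative. A non-significant result would be compatible with anything from no excess to a large one. Because safety stands in the primary aim and the participants are aged 3 to 18, the final safety statement should show how much excess risk the data leave open, and a p-value does not show that.

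**Working it through.** **Outcome wording, section by section**

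- 1.2: the aim is efficacy and safety; the hypothesis is efficacy only.
- 2.1: SCORAD is the primary outcome for both, and is described as a severity measure.
- 2.7: SCORAD is the primary outcome for efficacy.
- 2.10 and 2.13: safety is assessed by adverse events, laboratory tests and vital signs.

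Section 2.1 is the odd one out. The other sections show what is intended.

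**The article's own figure**

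There is no event rate, margin or sample size for safety to reproduce. The only sizing is on SCORAD change: difference 13.8 − 7.9 = 5.9, SD 8.2, 80% power, two-sided 0.05, 20% dropout. That gives 2 × (8.2 × (1.960 + 0.842) / 5.9)² = 30.3, so 31 per arm, and 31 / 0.8 = 38.75, so 39 per arm against the stated 30. This mismatch is a separate matter and nothing below depends on it. I take 30 per arm as the most the safety population can hold.

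**Power of the planned tests**

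Inputs: n = 30 per arm (section 2.7) and a two-sided level of 0.05 (sections 2.7 and 2.8). The event rates are assumptions, shown over a range. Power is the sum, over all pairs (a, b) with p ≤ 0.05, of Bin(a; 30, p₁) × Bin(b; 30, p₂). It is computed for Fisher's exact test and for the uncorrected Chi-square, since section 2.10 allows either.

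| Placebo v SSHT (assumed) | Fisher | Chi-square |
|---|---|---|
| 5% v 10% | 2% | 11% |
| 10% v 20% | 10% | 19% |
| 5% v 20% | 24% | 45% |
| 20% v 40% | 30% | 39% |
| 10% v 30% | 37% | 50% |
| 10% v 40% | 71% | 80% |
| 20% v 60% | 85% | 90% |

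A doubling of risk is usually missed by either test. Only very large absolute differences, of 30 points or more in this table, are detected reliably.

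**Results that need no assumed rate**

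- 5/30 on SSHT against 0/30 on placebo: Fisher p = 2 × C(30,5) / C(60,5) = 2 × 142,506 / 5,461,512 = 0.052, which is not significant. Six events are needed: 2 × C(30,6) / C(60,6) = 2 × 593,775 / 50,063,860 = 0.024.
- The same 5/30 v 0/30 table by uncorrected Chi-square: 60 × (5 × 30)² / (30 × 30 × 5 × 55) = 5.45, p = 0.020. The two permitted tests can therefore fall on opposite sides of 0.05.
- No events in 30: the exact two-sided 95% upper limit is 1 − 0.025^(1/30) = 11.6%.

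**The case against.** The strongest reply has three parts.

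*The SCORAD sentence is loose drafting.* The sentence just before it mentions adverse events, and sections 2.10 and 2.13 define a safety population, three safety domains, a testing schedule and a follow-up interview. A reader might infer from 2.1 that safety will be judged by SCORAD; the rest of the article rules that out. This stands. What remains is a wrong statement in the section that defines the outcomes, on half of the primary aim.

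*The harm supposes a conclusion that nobody has written.* A reader might infer that a non-significant test will be reported as showing SSHT to be safe. The article sets no rule for declaring safety, and its aim is only to evaluate it. This also stands, so no planned false conclusion can be charged.

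*Low power for adverse events is normal in a small trial sized on efficacy.* Chi-square or Fisher tests are conventional, and section 2.10 also plans summaries by body organ. That is fair, and it means that neither a larger trial nor a power target for safety is called for. Nor can one say that every tripling or quadrupling of risk would be missed: Fisher power reaches 71% for 10% v 40% and 85% for 20% v 60%. Reducing the denominator by the 20% dropout would be wrong too, because the safety population keeps anyone with one dose and one later safety assessment.

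Interval estimates could be left to a fuller plan, and their absence alone would be no finding. The article does, however, fix a significance test as its between-group safety method while placing safety in the primary aim.

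**Conclusion.** The point holds in a limited form. Section 2.1 misassigns SCORAD to safety and is contradicted by sections 2.7, 2.10 and 2.13, although safety will in practice be measured by suitable means.

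The fixed between-group safety test is weak evidence when non-significant. For excesses of 5 to 20 points its power is 2% to 37% by Fisher and 11% to 50% by Chi-square. It becomes adequate only for much larger differences. These percentages rest on assumed event rates, because the article gives none. The p = 0.052 for 5/30 v 0/30 and the 11.6% upper limit for 0/30 need no assumed rate, only a full 30 per arm; fewer assessed children would widen the limit.

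This limits what can be inferred about safety. It does not affect the efficacy analysis.

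**What to change.** In section 2.1, restrict SCORAD to efficacy and name adverse-event incidence, together with laboratory abnormalities, as the safety outcome.

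In section 2.10, make the basis of the safety statement the incidence per arm and the risk difference, each with an exact 95% confidence interval. Keep any Chi-square or Fisher test as supplementary, and state that a non-significant result will not be taken as evidence of safety.

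The cost is a change of wording in two sections and some added interval output. No new data, visits or participants are needed. The downside is a more cautious safety statement, because the intervals will be wide.

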**Figure 1 F1:**
[figure not shown]
Study flowchart describing the details of the randomized controlled trial. The entire trial includes assessments on week 1, week 4, and week 8 (follow-up visit).

**Table 1 T1:**
[figure not shown]
Schedule of enrolment, interventions, and assessments.

### Participants

2.2

#### Recruitment

2.2.1

Recruitment of the participants began in September 2017 at the Won-Kwang University Korean Medicine Hospital and is expected to finish in August 2020. The advertisement to recruit participants for this clinical trial includes notices on bulletin boards in commercial buildings, apartments, hospitals, and on the streets. Written consent will be obtained from all participants before registration, and participants may withdraw from the trial at any point in time without penalties. The written consent form includes information regarding the background and purpose of the study, trial drug and placebo drug, outcome, and the expected benefits and drawbacks.

#### Inclusion criteria

2.2.2

Participants should meet all of the following inclusion criteria:

1.Males and females aged 3 to 18 years with SCORAD scores between 15 and 49, exhibiting ≥3 main and ≥3 accessory symptoms based on the diagnostic criteria developed by Hanifin and Rajka2.Participants with ≥1 box checked for gastrointestinal symptoms or food allergy history, in the questionnaire survey for gastrointestinal disorders3.Participants who have fully understood the information provided about the study voluntarily decided to participate and agreed to comply with the precautions (written consent is required from the participants’ parents)

#### Exclusion criteria

2.2.3

1.Patients receiving treatment for severe AD (antihistamines, adrenocortical hormones, Korean traditional herbal medication)2.Patients who have previously used oral antihistamines, steroids, antibiotics, systemic photochemotherapy, and other immune suppressants in the previous 4 weeks3.Patients with systemic infections or under treatment with systemic antibiotics4.Patients with severe dermatological disorders aside from AD, pigmentation, or large scarring of the area affected by AD5.Patients currently receiving interferon (IFN) drug treatments (IFN-α, IFN-β)6.Patients with liver diseases (liver cirrhosis, liver cancer)7.Patients with platelet count ≤100,000/mm^3^ due to chronic hepatitis-induced liver dysfunction8.Patients with kidney diseases (acute/chronic renal failure, renal syndrome)9.Patients with acute severe cardiovascular diseases (cardiac failure, myocardial infarction, cerebral infarction)10.Patients with a history of antipsychotic drug use within 2 months before the screening examination11.Patients who have participated in other clinical trials within the past 4 weeks12.Patients with a history of hypersensitivity or allergic reaction to an ingredient of the clinical trial product or the product itself13.Patients with a history of drug or alcohol abuse14.Patients who are pregnant or breastfeeding15.Patients who may become pregnant and have not used appropriate contraceptives (excluding those who have undergone sterilization surgery)16.Patients who are judged ineligible to participate in the trial by the principal investigator for other reasons, including diagnostic radiology outcomes

### Study phase

2.3

When patients visit the trial center for the screening process, they will undergo different assessments, including blood and urine tests, and answer a survey questionnaire on AD symptoms by which the investigator may determine the patient's eligibility to participate in this clinical trial. At the screening visit, Lacticare (hydrocortisone-acetate 1% (100 g)) will be provided as a control variable which is the conventional therapy of AD to all participants. The amount and frequency of ointment usage from the screening visit to visit 3 (8-week time point) will be recorded. Patients found eligible to participate will be informed of their eligibility via a telephone call, and selected participants will be asked to visit the trial center (visit 1) within 2 weeks of the screening examination for random assignment into either the experimental group or the control group. After the assignment, the participant will undergo additional assessments (answering survey questionnaires including those on AD, as well as a physical examination) and will receive enough of the trial product for 4 weeks (to be used 3 times per day). After 4 weeks, participants will be asked to return for visit 2 to perform identical assessments (survey questionnaires and blood tests). For the following 4-week period, the participants will be asked to stop the usage of all medication, with the exception of Lacticare, and return for visit 3 after 4 weeks to undergo the same assessment. Detailed assessment types and the schedule used are outlined in Table 1.

### Intervention

2.4

Participants in the experimental and control groups will be required to take SSHT or the placebo product, respectively, for 4 weeks, 3 times a day before each meal. The dosage for different age groups is as follows: 4.5, 6, and 9 g/day for participants aged 3 to 5, 6 to 13, and 14 to 18 years, respectively. Both the SSHT and the placebo were manufactured by Hanpoong Pharm. Co Ltd., according to Korea Good Manufacturing Practice standards. Notably, both SSHT and placebo are of identical color, dosage form, and appearance (dark brown granules). The SSHT consists of 2.33 g Bupleuri Radix, 1.7 g Pinelliae Rhizoma, 1.33 g Zingiberis Rhizoma Recens, 1.00 g Scutellariae Radix, 1.00 g Zizhyphi Fructus, 1.00 g Ginseng Radix, 0.67 g Glycyrrhizae Radix et Rhizoma, 1.31 g lactose hydrate, and 0.315 g corn starch. The placebo consists of 2.57 g corn starch, 0.358 g lactose hydrate, 0.05 g citric acid hydrate, 0.02 g caramel colorant, and 0.0002 g ginseng flavor powder. Both SSHT and the placebo groups will receive Lacticare (hydrocortisone-acetate 1% (100 g)) for the entire duration of the trial from the screening point (12 weeks) as a control variable.

### Randomization

2.5

Participants who provide written consent to participate in this clinical trial will be assigned screening numbers in the chronological order of consent received. Participants deemed eligible according to the inclusion/exclusion criteria will be assigned a random number in the order of their visit date. Additionally, the Strategic applications software (SAS, software version 9.3) will be used to assign the participants randomly to either the experimental group or the control group. A method of block randomization, involving the use of a set assignment ratio (1:1) within identically sized blocks (i.e., 4, 6, or 8 participants per block), will be used. Before the start of the clinical trial, the research pharmacist at the trial center will provide the participants with a box containing the trial product, and the number on the box will match the participant's random assignment number.

### Blinding

2.6

In order to obtain reliable data from the clinical trial, double-blinding is performed so that neither the investigator nor the participants know which participant is assigned to which group. Double-blinding will be maintained unless a medical emergency occurs. Data locking will be maintained for information regarding the group assignment and will be made publicly available at the time of statistical analysis after the completion of the clinical trial. In case of cessation of double-blinding for different reasons, such as an adverse event, the appropriate procedure will be followed to report the incident to the Institutional Review Board (IRB) and to notify the sponsor.

